## Abstract

**Background:**

Giving up driving is a pivotal life event and universal challenge for people living with dementia and their families, and a complex area of clinical practice for health professionals who monitor driving cessation. The best outcomes are for individuals to plan for and eventually cease driving, however with insufficient support programs in place, many avoid the issue until it is reaches a crisis point. This program of research investigates a comprehensive support- and education-based intervention targeted at people living with dementia and their care partners who are managing driving cessation. The primary aim of this research is to determine the effectiveness of the program through a cluster randomized controlled trial.

**Methods/design:**

The intervention (CarFreeMe) is an intensive program delivered by a trained health professional that addresses practical and emotional needs relevant to driving cessation. The seven module program is person-centred, covering awareness raising, adjustment, and practical support that is individualized according to geographic location and the particular goals and preferences of participants. A cluster randomized controlled trial will evaluate the effectiveness of the program. Evaluation will take place pre-intervention, immediately following, and three months post-intervention. Clusters are randomized to either intervention or usual treatment. Participants within clusters will be recruited via primary and secondary care clinics, community agencies, service providers, local media, social media, support groups, and word of mouth. The primary outcome measure for persons with dementia and their care partners is lifespace, collected via (i) smartphone GPS technology and (ii) self-reported number of episodes away from home (during the past week). Secondary outcomes include safe alternative transport status, wellbeing, depression, anxiety, and self-efficacy, which will be collected from dyads. Caregiving strain will be collected from care partner/family member only. A process evaluation of the intervention will also be undertaken.

**Discussion:**

There is an urgent need for therapeutic approaches to supporting people living with dementia and their families to negotiate the complex decision making involved in deciding to change their approach to driving. The driving cessation intervention may fill an important gap in service delivery to people living with dementia who are adjusting to life without driving.

**Trial registration:**

Australian and New Zealand Clinical Trials Registry ACTRN12618000388213, 15 March 2018.

## Background

Stopping driving impacts the health and quality of life of people with dementia and their care partners. It also poses considerable challenges to health professionals who monitor driving issues and to those involved in testing and licensing. Without intensive practical and emotional support to plan for, and eventually, cease driving, people with dementia are at high risk for increased depression, anxiety, grief, social isolation, unsafe and unlicensed driving and injury. We have developed a comprehensive support- and education-based intervention targeted at people with dementia and their care partners and family members to manage driving cessation. The intervention is a translation of a proven driving cessation intervention for people without cognitive decline and has been trialled in an intensive case study. This project investigates the effectiveness of the evidence-based driving cessation intervention for people with dementia and their family members who are retiring from driving, through a cluster randomized controlled trial.

A diagnosis of dementia does not mean the immediate cessation of driving [1, 2]. However, at some stage people with dementia will need to stop [3]. Without necessary support programs in place, many people living with dementia avoid the issue until it is reaches a crisis point [4]. Health professionals acknowledge the complexity of driving and driving cessation issues for people with dementia, and studies identify that their lack of knowledge and confidence in managing driving cessation issues may lead to reluctance to do so [5]. Some drivers with dementia avoid their responsibility to stop driving even when their licence is terminated for emotional, logistical, and mobility reasons, or due to a lack of insight and awareness of the dangers [2, 4, 6]. Driving cessation can diminish ‘lifespace’ – defined as the extent of movement through the environment that captures lived community mobility [7] – constricted lifespace may lead to more rapid cognitive decline [8–10].

Timing of the decision to stop driving is critically important. If the decision to cease driving is delayed, then loss of insight into declining driving abilities exacerbates the challenges of stopping [3]. The best outcome is for people with dementia and their care partners to plan early, and eventually cease driving. However, it is an extremely personal and difficult issue for people with dementia, and one that care partners and families fear confronting [11]. Furthermore, with limited available information about how to evaluate fitness-to-drive in primary care, and no practical interventions for people with dementia, it is a poorly resourced area of clinical dementia care. Despite the concerns for safety and recognition of the impact of driving cessation on quality of life, health and wellbeing of people with dementia and their care partners, there are currently no theory-driven, empirically tested interventions to facilitate driving cessation for people with dementia in routine clinical practice within Australia. The CarFreeMe (for people with dementia) intervention aims to fill the gap.

### Preliminary work

The researchers have developed a comprehensive support and education-based driving cessation intervention, which is a translation of an effective community-based psychosocial intervention for people *without* cognitive decline: ‘CarFreeMe’ (formerly known as UQDRIVE) [12]. The translated intervention is aimed at the unique needs of drivers with dementia and their families. The effectiveness of the original CarFreeMe program, aimed at improving outcomes of driving cessation for older people without cognitive decline, has been systematically explored with a general older adult population in a randomized controlled trial [13]. The dementia specific intervention was pilot tested with a sample of drivers with dementia who had stopped driving and their family members in Brisbane, Queensland Australia [unpublished thesis]. Improvement in community mobility outcomes, self-efficacy [13], individualized transport and lifestyle goals [14], and high levels of satisfaction [15] have been reported by participants within CarFreeMe programs. The current program of research will implement a cluster randomized controlled trial (cRCT) examining face-to-face delivery of the dementia specific intervention to people living with dementia in the community, in Queensland, Australia.

### Aims and objectives

The primary aim of this study is to assess the impact of participating in the CarFreeMe intervention on lifespace compared to usual care, for people with dementia. The secondary aim is to assess the impact of CarFreeMe on quality of life, wellbeing, and self-efficacy for people with dementia and their care partners, compared to usual care.

The objectives are to:Maintain or increase community mobility outcomes for people with dementia who are transitioning to driving cessation (or have recently ceased driving);Increase use of safe alternative modes of transport;Evaluate the impact of the intervention on self-efficacy, wellbeing, and community participation of people with dementia;Evaluate the impact of the intervention on self-efficacy, wellbeing, and community participation of the care partners/family members of people with dementia.

It is predicted that compared with usual care, the driving cessation intervention:Maintains or increases *lifespace* – as measured by metrics collected via a custom Smartphone app;Maintains or increases *episodes away from home* and using safe modes of transport – as measured by metrics collected via Smartphone and App, and self-report;Results in participants:greater self-efficacy in dealing with driving cessation decision making;higher measures of wellbeing;decreased measures of depression, anxiety, isolation, and stress.

## Methods

### Design

A cluster randomized controlled trial will be conducted with regions (electoral districts) used as the unit of randomisation, to minimize the risk of contamination between conditions. Cluster randomisation aims to also address possible attrition, as participants will not be made aware of an alternative group. Clusters will be matched so that pairs of regions are as similar as possible on demographics, and potential local area transport and health infrastructure, to increase efficiency [16]. Clusters will be randomized using concealed allocation to either the intervention or waitlist control group. Randomisation to treatment or wait-list control condition will occur before baseline measurement. During a period of baseline data collection, no cluster will be exposed to the intervention. After baseline, one will proceed to the intervention arm, while the other will proceed to the wait-list ‘treatment as usual’ (ie. no intervention, written information, pamphlets) control arm – to receive the intervention at a later time (after Time 3, see Fig. 1).

**Fig. 1 Fig1:**
[figure not shown]
Abridged CONSORT diagram

### Study setting

The study will be set in the general community in Queensland and Northern New South Wales, Australia.

### Participants

#### Eligibility criteria

*Persons with dementia* will be older people (aged 65 years and over), male or female, with mild cognitive impairment or mild or moderate dementia of any type, and driving or driving cessation is a current issue for them. Persons living with dementia will be able to provide informed consent to participate or (where determined necessary) to have a care partner that can provide proxy informed consent on their behalf. People with a diagnosis of younger-onset of dementia are excluded from this study because the program has not been translated for people with younger-onset dementia as yet. Non-English speaking participants will be excluded from participating because the intervention at present does not cater to a non-English speaking audience. Potential participants with dementia will be screened using the Clinical Dementia Rating scale (CDR) [22]. Participants with scores of 2 or less will be eligible to participate (0.5 = very mild dementia, 1 = mild dementia, 2 = moderate dementia).

*Care partners/support persons* self-identified informal primary care partners of the retired/retiring driver with dementia are eligible to participate alongside that person. To be eligible support persons may be male or female, and must be aged 18 years and over, have the ability to communicate in English, and be providing ongoing support to the person with the dementia.

### Intervention description

CarFreeMe-for People with Dementia was developed in accordance with the four stages of the Medical Research Council’s framework (2000) for investigating health-related complex interventions. Stage 1 has been conducted in the preliminary work undertaken to identify the issues for driving cessation for people with dementia and their care partners. This informed the development of the seven-module CarFreeMe for People with Dementia intervention (see Table 1). The content, language, format and activities were adapted from a proven driving cessation intervention for people without cognitive decline [13] for people with dementia and additional modules created for family members – whose involvement is key. The adaptation was reviewed by an expert reference group and preliminary evaluations conducted within an intensive case study model. The CarFreeMe for People with Dementia intervention is designed to be person-centred and flexible in content and delivery, e.g. in-home, one-to-one, dyads, or small group settings. As part of its design, the intervention is individualized according to geographic location and the needs of participants. For example, older adults are encouraged to consider future transport arrangements, plan for lifestyle changes, form realistic expectations of life changes after driving cessation, and practice using alternative transport. Importantly, they are supported in their emotional adjustment to the role loss. The individualized program involves a combination of one-to-one sessions, groups, practical outings and activities with a local experienced health professional, as well as some home-based independent activities.

**Table 1 Tab1:** Structure and content of the intervention for people living with dementia

Modules	Title and contact examples
Module 1	Living with dementia: focuses on the changes that may occur with dementia, and strategies to live positively.
Module 2	Balancing independence and safety: provides information about driving safety in later life and things for consideration regarding retirement from driving.
Module 3	Adjusting to losses and changes: covers changes that may occur to lifestyle and feelings of loss and grief that may result from retiring from driving. It also includes strategies to use to help with adjusting.
Module 4	Experience of retiring from driving: covers what it can be like to give up driving. Stories from other retired drivers and family members are included to highlight different ways that people have adjusted to giving up driving.
Module 5	Alternative transport: covers the range of alternatives to driving that may be useful and ideas of where to find out more.
Module 6	Lifestyle planning: covers things to consider in planning for achieving a balanced lifestyle.
Module 7	Advocacy and support: focuses on the services that are available to participants and the steps to take to improve the service/s, and to make service providers aware of these needs.

The intervention includes seven modules that cover education and practical support, delivered by a health professional who is trained in, for example, occupational therapy, psychology, social work or nursing, and who is experienced in working in community care with older adults living with dementia and their family members. It is anticipated that trained health professionals will deliver the intervention to people with dementia and their families in their homes and/or community settings, in individual, or group sessions, or a combination of both – depending upon participant preference.

Data collection will be conducted face-to-face with the person with dementia and their care partner by a research assistant who is blinded to the treatment condition that participants are randomized to.

### Control condition/comparator

Participants assigned to the control condition will receive ‘as usual’ treatment, which will include provision of information leaflets, for example information regarding driving and dementia and contact details of service providers.

### Recruitment and implementation plan

#### Participant timeline

The intervention includes seven modules that take approximately 60–90 min to deliver, and at least one practical outing. Three temporal measurement phases are involved in the trial. These include week one baseline assessment (Time 1), week 8 first follow-up post-intervention (Time 2), and three-month follow up (Time 3) approximately week 20, as shown in Fig. 1. Clusters will be randomized to the sequence of treatment (i) Baseline > Intervention > Follow up, or (ii) Baseline > Control > Follow up > Intervention), as shown in Fig. 1. That is, participants in the wait-list control group will be offered the driving cessation intervention after the three-month follow up assessment.

#### Sample size

The sample size calculation for this study used a power analysis applying the mean, and standard deviation (SD), and the minimum detectable difference between populations means = 1, for episodes away from home, obtained from a background study [13]. Allowing for 20% dropout and assuming detectable difference = 1, *SD* = 3.16 and ICC = 0.05. For 80% power with alpha set at 0.05, and the minimum detectable difference between population means, then with an average of 15 dyads per cluster, the minimum number of clusters required is 10. However, more clusters will be included to reach a minimum sample size.

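### The stated minimum of 10 clusters does not follow from the stated inputs: they require about 36 clusters (42 with 20% dropout), and 10 clusters give roughly 25–30% power, not 80%

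*Protocol article*

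**What the plan says.** The whole calculation stands in one paragraph of the protocol article (Sample size). The target is "the minimum detectable difference between populations means = 1, for episodes away from home". The SD is 3.16 and the ICC 0.05. Attrition and the error rates are given as "Allowing for 20% dropout and assuming detectable difference = 1" and "For 80% power with alpha set at 0.05". The result is that "with an average of 15 dyads per cluster, the minimum number of clusters required is 10". The paragraph then closes: "However, more clusters will be included to reach a minimum sample size". Neither that number of clusters nor that sample size is stated.

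The Design section describes a parallel comparison of paired regions: "After baseline, one will proceed to the intervention arm, while the other will proceed to the wait-list" control arm. On pairing it says "Clusters will be matched so that pairs of regions are as similar as possible on demographics", with efficiency as the reason. The sample size paragraph includes no matching correlation, no baseline correlation and no gain from repeated follow-up.

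**The concern.** The paragraph prints both its inputs and its output, so it can be checked directly, and the shortfall shows before any cluster formula is used. Ten clusters of 15 enrol 150 dyads, or 120 after 20% dropout. Individual randomisation with the same difference and SD would already need 314 analysed dyads, and clustering can only raise that number unless some other gain is assumed.

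Episodes away from home is one of the two measures of the main outcome and the only one used to size the trial. A trial run to the stated floor would more likely than not miss the difference it was designed to detect, and its null result would be read as if the design had had 80% power.

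**Working it through.** **Inputs (Sample size section).** Difference d = 1; SD = 3.16, so variance = 9.986; ICC = 0.05; m = 15 dyads per cluster; dropout 20%, so 12 of 15 analysed; power 80%; alpha 0.05. Sidedness is not stated, so two-sided is assumed here and one-sided is tried below. Equal allocation follows from the paired design.

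**Clusters required (normal approximation).**
- Individuals per arm: 2 × (1.960 + 0.842)² × 3.16² / 1² = 156.8, so 157 per arm and 314 in total.
- 15 analysed per cluster: design effect 1 + 14 × 0.05 = 1.70. 156.8 × 1.70 = 266.5 per arm; / 15 = 17.8, so 18 per arm and **36 in total** (540 dyads).
- 12 analysed per cluster: design effect 1 + 11 × 0.05 = 1.55. 156.8 × 1.55 = 243.0 per arm; / 12 = 20.2, so 21 per arm and **42 in total** (42 × 15 = 630 dyads enrolled).
- With a t reference on 2(k − 1) df, k being clusters per arm, 18 × 15 gives 78.2% power and 21 × 12 gives 79.5%. One more cluster per arm is then needed: 38 and 44 in total.

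**Power at the stated minimum.** SE = √(2 × 9.986 × design effect / dyads analysed per arm).

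| Clusters | Analysed per cluster | SE | Power, normal | Power, t |
|---|---|---|---|---|
| 10 in total (5 per arm) | 15 | 0.673 | 32% | 26% |
| 10 in total (5 per arm) | 12 | 0.718 | 29% | 23% |
| 20 in total (10 per arm) | 15 | 0.476 | 56% | 51% |
| 20 in total (10 per arm) | 12 | 0.508 | 50% | 46% |

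**Detectable difference with 10 clusters at 80% power.** Normal approximation: 2.802 × 0.673 = 1.88 and 2.802 × 0.718 = 2.01. With t on 8 df: about 2.15 and 2.30.

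**Attempts to reproduce 10 as a total.**

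| Reading | Clusters in total |
|---|---|
| One-sided alpha | 28 (m = 15) or 32 (m = 12) |
| Both dyad members counted as separate observations (m = 30) | 26 |
| ICC ignored, no dropout (156.8 / 15 = 10.45 per arm) | 21–22 |
| Pairing removes all between-cluster variance, no dropout (9.9 per arm) | 20 |
| 3.16 taken as a variance, two-sided (5.6 or 6.4 per arm) | 12–14 |
| 3.16 taken as a variance, one-sided, no dropout (4.4 per arm) | 10 |

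Only the last row reaches 10, and it contradicts both the printed SD and the stated dropout allowance. Leaving out the factor 2 at m = 12 also returns 10.1, but that is a one-sample formula and not a comparison of two arms.

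**The case against.** The best defence is that the design has features that buy precision: paired regions, a baseline measurement, two follow-ups and random-intercept models. Some combinations do lead to about 10 clusters per arm:

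- pairing that removes all between-cluster variance (9.9 per arm);
- baseline adjustment with a correlation of about 0.7 (9.1 to 10.3 per arm);
- two averaged follow-ups with baseline adjustment at correlations of 0.3 to 0.5 (8.9 to 11.3 per arm, assuming equal correlation between all time points).

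This stands as a possible account of where the figure came from. It does not support the figure as printed. The text does not say that 10 is per arm and lists none of these gains among its inputs, and full removal of between-cluster variance would cancel the ICC of 0.05 that it does list. For 10 clusters in total, a single-follow-up analysis would need a baseline correlation of about 0.85–0.87, and averaging both follow-ups would need about 0.8.

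A second objection is that 10 is only a floor and the protocol says it will be exceeded. That makes the harm conditional, but the sentence gives no number and still presents 10 as enough for 80% power.

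Third, 36 and 42 are not unconditional minima. They assume a two-sided test and the normal approximation, with no gain from pairing or baseline data. The figure of 42 also assumes that the 15 dyads are counted before dropout, which the text leaves open. This is fair and is carried into the verdict.

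**Conclusion.** The stated minimum is wrong as written. From the protocol's own inputs, 80% power needs about 36 clusters if 15 dyads per cluster are analysed and 42 if 12 are (38 and 44 on a t basis). Ten clusters give 23–32% power, and the difference they can detect is about twice the target.

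The figures assume a two-sided test, equal allocation and a single between-arm comparison without pairing or baseline gain. None of the single-assumption alternatives tried brings the total down to 10. A one-sided test lowers the requirement only to 28–32. Undisclosed precision gains could make about 20 clusters adequate, but only if they are stated and justified.

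**What to change.** Rewrite the sample size paragraph in one of two ways.

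1. **Correct the count.** With the stated inputs: 36 clusters (18 per arm, 540 dyads) before dropout, or 42 clusters (21 per arm, 630 dyads) with 20% dropout. Add one cluster per arm if a t reference is used.
2. **Keep the number of clusters that can be recruited** and state what it gives. For 10 clusters, that is about 25–30% power for a difference of 1 episode, or a detectable difference of about 2 episodes at 80% power.

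In either case, state whether the test is two-sided, whether the cluster count is a total or per arm, and whether 15 is counted before or after dropout. If a gain from pairing, baseline adjustment or two follow-ups was assumed, give the correlation used and its basis. Replace the closing sentence with a fixed number of clusters and dyads.

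The second option costs one reworded paragraph and a less favourable stated power, with no extra participants. The first commits the trial to a much larger number of regions.
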